### Ecological analysis

Treating the regions covered within the North West London ICBs as a random effect, mixed effects regression will be used to examine the effect of the rate of patients who died having EPaCCS on the annual rates of hospital deaths and time spent in hospital within the last 90 days of life, calculated, respectively, as the number of deaths with EPaCCS over total deaths, the number of in-hospital deaths over total deaths, and the aggregate time spent in hospital within the last 90 days of life over total deaths.^56^ Other approaches will be considered upon examining the data and the annual number of patients who died having EPaCCS.^33^

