North West London dataset	CMC records will be linked with the ‘Whole Systems Integrated Care’ (WSIC) dataset. WSIC is an electronic record used by healthcare professionals in North West London, which has a population of 2.4 million, to document essential information about patient care in the region (eight health boroughs, previously defined as CCGs).^65^ The WSIC dataset will include all individuals who have died in North West London within the timeframe spanning from 2010 to 2023. This linkage will allow the creation of two cohorts for comparison: individuals with EPaCCS (CMC) and those without EPaCCS. All decedents with a CMC record within the WSIC catchment area will be identified for inclusion within the linked dataset, while decedents without such records will form the control group. The WSIC dataset includes coded primary, secondary, acute, mental health, community health and social care data. This dataset also includes detailed information on social determinants of health, including ethnicity, and mortality data, including place of death. Cost data is also available as patient-level costs referring to the indicative spend calculated separately for each patient for each healthcare sector. This will be used in a cost minimisation analysis of EPaCCS, and it includes primary care level, acute, community, mental health and social care costs. Data linkage will be carried out by North West London Integrated Care Board and supported by existing data sharing framework.^66^ Figure 1 illustrates the data flow and linkage process. The linked dataset will be de-identified prior to being made available to the research team for the analysis

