
**Table 2 T2:** Mapping study objectives to data sources and eligibility to be included in analyses

Objectives		Data sources and eligibility
Work package 1		
1A	To describe and categorise the data fields and completeness of data contained within each EPaCCS register.	Anonymised EPaCCS data from London (CMC, n=140 000), Leeds (n=15 500) and Bradford (n=17 000)
1B	To describe the creation and content of EPaCCS records and elements relating to end-of-life decision-making preferences and ACP (ceiling of treatment, preferred place of care, and death and resuscitation status) in different regions across England.	
1C	To describe the socio-demographic and clinical characteristics of individuals who have created EPaCCS records in different regions across England.	
1D	To estimate associations between social determinants of health (socioeconomic position, ethnicity, age, and gender) and the completion of elements of ACP within EPaCCS.	
1E	To estimate associations between social determinants of health (socioeconomic position, ethnicity, age, and gender) and the creation of EPaCCS.	WSIC-CMC dataset of North West London deceased patients with/without EPaCCSLeeds decedent dataset 2021–2023 of deceased patients with/without EPaCCS
Work package 2		
2A	To explore the effect of EPaCCS on place of death and hospital use in the last 90 days of life.	WSIC-CMC dataset of North West London deceased patients with/without EPaCCSLeeds decedent dataset 2021–2023 of deceased patients with/without EPaCCS
2B	To explore the effect of an EPaCCS record on healthcare costs in the last 90 days of life.	WSIC-CMC dataset of North West London deceased patients with/without EPaCCS

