### Work package 2: evaluation of the effect of EPaCCS on place of death and secondary healthcare use at end of life and cost minimisation analysis of EPaCCS (objectives 2A and 2B)

The second work package will adopt a retrospective cohort design under a natural experiment framework to evaluate the effects of EPaCCS on quality indicators of end-of-life care. The quality indicators used in this work package include the place of death (primary outcome) and time spent in hospital in the last 90 days of life (secondary outcome).^48^ The hypothesis for work package 2 is that people with EPaCCS records are less likely to die in hospital and more likely to spend less time in hospital in the last 90 days of life compared with people without EPaCCS records. An EPaCCS record may address one or both sides of the cost-effectiveness ratio; reducing futile or unwanted treatments will save hospital resources while improving goal-concordant care realises more utility. However, there is also the potential for increased costs, notably through substitution effects, for example, if people die in a hospice instead of in a hospital. We therefore hypothesise that EPaCCS improve the cost-effectiveness of care near the end of life.

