Using the CMC-WSIC linked dataset and the Leeds dataset, the study will use a natural experiment approach^33^ and establish cohorts of patients who have died having EPaCCS (case) or not having an EPaCCS (control) in each dataset separately. Place of death will be coded as a binary variable for individual-level analysis, indicating whether death occurred in a hospital or elsewhere. For ecological analysis, rates of hospital deaths per year will be calculated for each one of the eight health boroughs (previously called CCGs) in North West London. Time spent in hospital will be derived as a continuous variable measuring the number of days between admission and discharge within the last 90 days of life, or between admission and death for patients who died in hospitals. Rates of time spent in hospital within the last 90 days of life per year will also be calculated. The cost analysis will use the patient-level cost data available in WSIC. Formal costs will be estimated by combining utilisation frequencies in the data with unit costs for different services.^49^ Informal care hours will be estimated from the literature on end-of-life care populations and associated costs using the substitution method (primary analysis) and opportunity cost method (sensitivity analysis). Intervention costs will be estimated using NHS data.^50^ We will model costs after diagnostic testing of different modelling approaches in the context of distributional characteristics.^51^

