### Creating comparative cohorts

This study will take an inclusive approach to defining the cohorts for inclusion in the individual-level analysis, identifying deceased patients who had mention of one of the four main disease-related causes of death in their clinical records within the last year of life (cancer, dementia, heart or lung disease). Based on previous analyses^52^ and publicly available national data,^53^ we hypothesise that 22–30% of the EPaCCS cohort will die in the hospital compared with 45–50% in the non-EPaCCS group. The inverse probability of treatment weighting will be used to account for the confounding resulting from the non-random allocation of EPaCCS to the groups and balance characteristics between cohorts.^54^ First, a multivariable logistic regression will be used to determine the propensity score weights. Factors included in the model to estimate propensity scores will include the confounders selected to be included in the main outcome analysis (such as age, sex, ethnicity, deprivation and primary diagnosis). These confounders will be cautiously selected based on thorough discussions with our team, which includes experts in palliative care, input from the patient and public involvement group with lived experience in end-of-life care, and a comprehensive literature search. Then, for each patient inpatient encounter, a weight defined as the inverse of the probability of the treatment they had received will be calculated. The balance of patients’ characteristics will be assessed visually and by examining the standardised mean differences.^55^

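### Hospital death and hospital time are analysed in four-disease decedents at individual level but over all deaths ecologically, with no reason given and no disease-mix term, so the ecological slope can be biased in either direction

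*Protocol article*

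**What the plan says.** In the protocol article, the opening section of work package 2 names "place of death (primary outcome") as the main quality indicator and time spent in hospital in the last 90 days of life as the secondary one. Both are analysed at individual and at area level.

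- **Individual level.** Under Creating comparative cohorts, the disease restriction is introduced as a way of "defining the cohorts for inclusion in the individual-level analysis". It selects decedents "who had mention of one of the four main disease-related causes of death in their clinical records", counting entries from the final year before death; the four are dementia, cancer, lung disease and heart disease. The same section lists primary diagnosis among the example confounders for the propensity score.
- **Area level.** The work package 2 text says that "rates of hospital deaths per year will be calculated for each one of the eight health boroughs" in North West London. Under Ecological analysis, the exposure and the main outcome are "the number of deaths with EPaCCS over total deaths, the number of in-hospital deaths over total deaths", and hospital time is also divided by total deaths. Region enters as a random effect. No covariate for diagnosis or disease mix is named, and other approaches are left open until the data are seen.
- **Data.** Table 1 confirms that all deaths are held: "The WSIC dataset will include all individuals who have died in North West London within the timeframe spanning from 2010 to 2023".

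No reason is given for using one population in one analysis and a different one in the other.

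**The concern.** Both analyses serve objective 2A and the same hypothesis, that people with EPaCCS are less likely to die in hospital and spend less time there. The plan treats diagnosis as a confounder for individuals but names nothing to handle it for borough-years. A borough-year with more deaths outside the four groups may have lower all-deaths coverage simply because fewer of its decedents are typical EPaCCS candidates. Its hospital-death rate also shifts if those other deaths occur in hospital more or less often. A regional random effect does not remove change in disease mix within a borough over the years.

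Two things are at stake. The slope may absorb part of the effect of disease mix. And if the ecological and individual results disagree, the plan has no analysis that shows whether the method or the population is responsible.

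**Working it through.** The plan states no ecological effect size, so there is no figure to reproduce. The check asks when the all-deaths denominator alters the slope, and by how much.

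**Inputs from the protocol.** Expected hospital death is 22-30% with EPaCCS and 45-50% without. The mid-points are 26% and 47.5%, so d = 0.475 - 0.26 = 0.215. There are eight boroughs. With 13 years (2010-2022, the life of the London register) or 14 years (2010-2023, the linked deaths), that is 8 × 13 = 104 or 8 × 14 = 112 borough-years.

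**Assumptions, not in the protocol.** Mean share of deaths outside the four groups 0.30, with SD 0.03 or 0.05 between borough-years; hospital-death rate in those deaths δ = 15 points above or below four-disease decedents without EPaCCS; no EPaCCS in those deaths; a constant effect d; simple regression without the random effect.

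**Formula.** Let u be the share outside the four groups, c the coverage within them and p0 = 0.475. Then:

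- coverage over all deaths: E = (1 - u)c
- hospital-death rate: H = (1 - u)(p0 - dc) + u(p0 + δ) = p0 - dE + δu
- slope of H on E = -d + δ × cov(u, E) / var(E)

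The second term is the bias. It is zero if u is constant or δ = 0, so the wider denominator alone does no harm.

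**Case 1: mix independent of coverage.** Here cov(u, E) = -mean(c) × var(u), and var(E) = 0.70² var(c) + mean(c)² var(u) + var(u)var(c).

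Worked example with mean coverage 0.35, SD(c) = 0.05 and SD(u) = 0.05: cov = -0.35 × 0.0025 = -0.000875; var(E) = 0.001225 + 0.000306 + 0.000006 = 0.001538; ratio = -0.569. The bias is 0.15 × 0.569 = 0.085 in size, and 0.085/0.215 is about 40%.

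| SD of coverage | SD of mix | Slope, δ = -0.15 | Slope, δ = +0.15 | Relative bias |
|---|---|---|---|---|
| 0.05 | 0.03 | -0.180 | -0.250 | 16% |
| 0.05 | 0.05 | -0.130 | -0.300 | 40% |
| 0.10 | 0.03 | -0.206 | -0.224 | 4% |
| 0.10 | 0.05 | -0.190 | -0.240 | 12% |
| 0.15 | 0.03 | -0.211 | -0.219 | 2% |
| 0.15 | 0.05 | -0.203 | -0.227 | 5% |

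**Case 2: steady roll-out, mix unrelated to time.** Let coverage rise from 0 to 60% over 13 years, with borough noise of SD 0.05. The yearly values have SD 0.187, so SD(c) = √(0.187² + 0.05²) = 0.194 and mean(c) = 0.30. The bias is 0.0022 at SD(u) = 0.03 (1.0%) and 0.0060 at SD(u) = 0.05 (2.8%).

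**Case 3: mix trends with roll-out.** Coverage over all deaths rises by about 0.70 × 0.60 = 0.42. A 5-point drift in u gives 0.15 × 0.05/0.42 = 0.018, or 8%. A 10-point drift gives 0.15 × 0.10/0.42 = 0.036, or 17%.

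**Wider inputs.** With SD(c) = SD(u) = 0.05, mean coverage 0.30, a 17.5-point rate gap and a correlation of ±0.5 between mix and coverage, the slope ran from -0.071 to -0.358. The 40% figure is therefore not a ceiling under every assumption.

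**The case against.** The strongest reply is that there is no contradiction. The restriction is expressly scoped to the individual-level analysis, the ecological section expressly says total deaths, and exposure and outcome share one denominator. All-deaths coverage against all-deaths hospital mortality is a legitimate area-level estimand. Table 2 sets no disease limit for objective 2A, which fits an objective containing both analyses. All of that stands, and Table 2 needs no correction.

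A reader might infer two stronger conclusions that the protocol does not support.

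- **That the ecological slope is biased.** The protocol gives neither the variation in disease mix nor hospital-death rates by disease. The cohort is defined by a mention in the records, not by certified cause of death, so the excluded share is unknown and may be small. Roll-out from 2010 and the rise in London records after March 2020 suggest wide variation in coverage, where the bias is small unless the mix trends too.
- **That the two results cannot be compared because of their denominators.** With a stable mix the ecological slope equals the individual risk difference. Comparison is limited in any case: one result is a borough-year slope and the other a marginal odds ratio, and the individual analysis also uses Leeds. The protocol does not say the two will be pooled or used to corroborate each other.

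It can also be said that restricting the rates is no cure. With two subgroups inside the four-disease cohort (assumed 30-point coverage gap, 15-point hospital-death gap, share SD 5 points), the restricted slope is -0.257 at coverage SD 5 points and -0.226 at 10, against -0.215. This is right, and it is a reason to add the restricted analysis rather than replace the all-deaths one.

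Finally, covariate detail can be left to the statistical analysis plan. But the denominators are written out here. The planned sensitivity analysis on cohort identification is not said to align the ecological rates, and openness to other approaches commits to nothing.

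**Conclusion.** The point holds in a conditional form. The protocol analyses place of death and hospital time in two populations without explanation, and its ecological model names no term for disease mix although diagnosis is treated as a confounder for individuals. This can bias the ecological slope in either direction.

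Under the assumed inputs, the bias is about 1-3% with wide coverage variation and a mix unrelated to time, and about 8-17% with a mix that trends 5-10 points alongside roll-out. It is about 15-40% when the coverage left to explain has an SD of only 5 points, which could also arise if period is adjusted for. It is zero with a constant mix or equal hospital-death rates. Which case applies cannot be told from the protocol, but the linked data would show it. If EPaCCS also reaches the other deaths and works differently there, the all-deaths slope answers a different question; that is a change of estimand, not a bias.

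**What to change.** Amend the Ecological analysis section in three ways.

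1. State that the all-deaths rates are an area-level estimand for all North West London decedents, and why that population was chosen.
2. Add the borough-year share of deaths outside the four disease groups as a covariate in that model.
3. Prespecify a companion analysis in which EPaCCS coverage, hospital deaths and hospital time are all computed among the four-disease decedents defined under Creating comparative cohorts. A disagreement with the individual-level result can then be attributed to method or to population.

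The data are already in the linked dataset, so the work is one filter, one covariate and a wording change. The costs are one extra parameter on about 104-112 borough-years, smaller denominators in the companion analysis, and dependence on how completely the four diseases are recorded, which may vary by year or by EPaCCS status. The companion analysis does not remove confounding by mix within the four diseases, and the report should say so.

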### Missing data considerations

Individual-level missing data of the primary outcome variable (place of death) will be excluded from the multivariable analysis. However, in handling missing data related to covariates, those with incomplete data will be identified for a thorough characterisation of the missingness. Depending on the type of data and the level and mechanism of missingness, individual patients without matching covariate data may be excluded from the multivariable modelling. In doing so, we would also be mindful that by excluding such patients, modelling could be subject to biases, for example, due to under-reporting. Hence, we may consider imputing missing data, with sensitivity analysis to determine the effectiveness of imputation on the model outputs.

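### The ecological hospital-death rate divides by all deaths, so read literally a death of unknown place acts as a non-hospital death, while the individual-level analysis excludes it

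*Protocol article*

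**What the plan says.** Place of death is the primary outcome of work package 2. For the individual-level analysis the work package 2 section states: "Place of death will be coded as a binary variable for individual-level analysis, indicating whether death occurred in a hospital or elsewhere". No category for unknown place is described. Missing data considerations then says: "Individual-level missing data of the primary outcome variable (place of death) will be excluded from the multivariable analysis".

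For the ecological analysis, "rates of hospital deaths per year will be calculated for each one of the eight health boroughs" in North West London. The Ecological analysis section gives the formulas. The exposure is "the number of deaths with EPaCCS over total deaths", the primary outcome is "the number of in-hospital deaths over total deaths", and hospital time in the last 90 days is also divided by total deaths. The North West London entry of Table 1 describes the population behind those totals: "The WSIC dataset will include all individuals who have died in North West London within the timeframe spanning from 2010 to 2023".

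The article gives no expected proportion of deaths with unknown place. Its Analysis section for work package 1 plans imputation of missing key outcomes. That rule sits under the other work package and is not counted here as a conflict.

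**The concern.** One objective (2A) has two analyses of the same outcome, and their stated rules treat the same decedent differently. A person with no recorded place of death leaves the individual-level model. In the ecological formula the same person stays in the divisor and can never be counted above the line, which has the effect of a non-hospital death.

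The ecological model relates the hospital-death rate to EPaCCS coverage across boroughs and years. Anything that changes the share of unknowns alongside coverage therefore feeds into the estimated EPaCCS association. The section describes a random effect for area and names no calendar-time term. A time term may be added in the analysis plan, but it would not remove drift that differs between boroughs.

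**Working it through.** The plan states no figure to reproduce. The missing fractions and coverage values below are assumptions.

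**Inputs.** Hospital-death shares come from Creating comparative cohorts: 22–30% with EPaCCS, 45–50% without (midpoints 26% and 47.5%). They refer to the individual-level cohort defined by four disease groups, so they only illustrate the all-deaths rate. Let m be the fraction with unknown place, p the hospital share among known-place deaths, and q the hospital share among unknowns. Subscripts E and N mean with and without EPaCCS.

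**1. Level of the rate.**
- True rate: p(1 − m) + qm.
- Rate over total deaths: p(1 − m), with bias −qm.
- Rate over known-place deaths: p, with bias m(p − q).

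With p = 40% and m = 5%:

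| q | True rate | Over total deaths (bias) | Over known place (bias) |
|---|---|---|---|
| 0% | 38.0% | 38.0% (0) | 40.0% (+2.0 points) |
| 40% | 40.0% | 38.0% (−2.0 points) | 40.0% (0) |
| 100% | 43.0% | 38.0% (−5.0 points) | 40.0% (−3.0 points) |

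The total-deaths rate is never too high. The known-place rate is exact only when q = p. The formula as written equals the bound in which every unknown is assigned to elsewhere; the opposite bound is p(1 − m) + m, here 43.0%.

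**2. Slope on coverage, equal missingness.** If place is missing at random within each group, the slope from 0% to 100% coverage is p_E(1 − m_E) − p_N(1 − m_N). With m_E = m_N = m this is (1 − m)(p_E − p_N). At the midpoints the true slope is 0.26 − 0.475 = −0.215. It becomes −0.213 at m = 1%, −0.204 at 5% and −0.194 at 10%.

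**3. Slope, missingness differing by EPaCCS status.**

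| Shares E / N | True slope | m_E = 1%, m_N = 10% | m_E = 10%, m_N = 1% |
|---|---|---|---|
| 30% / 45% | −0.150 | 0.297 − 0.405 = −0.108 (28% too small) | 0.270 − 0.4455 = −0.176 (17% too large) |
| 22% / 50% | −0.280 | 0.2178 − 0.450 = −0.232 (17% too small) | 0.198 − 0.495 = −0.297 (6% too large) |

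The known-place denominator does better here but is not exact. At 50% coverage with 30% and 45%, the true rate is 37.5%. With m_E = 1% and m_N = 10%, total deaths give 35.1%. Known-place deaths give 0.351 / 0.945 = 37.1%.

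**4. Drift over time.** At 50% coverage the midpoint rate is (26% + 47.5%) / 2 = 36.75%. If m fell from 10% to 2%, the measured rate would rise by 0.08 × 36.75% = 2.9 points with no change in care. For scale, a 20-point rise in coverage is worth 0.20 × 21.5 = 4.3 points and a 40-point rise 8.6 points. Nothing in the document indicates such a drift; the example shows only that the mechanism is not trivial if m moves.

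**5. A repair that would not work.** Suppose acute records are used to recover hospital deaths among the unknowns, and the remaining unknowns are then dropped. With a true rate of 47.5%, m = 10% unrelated to place and full recovery, the rate becomes 0.475 / (0.90 + 0.10 × 0.475) = 0.475 / 0.9475 = 50.1%, or 2.6 points too high. If every unknown is instead classed one way or the other and kept in the denominator, the rate is 47.5%.

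**The case against.** The strongest reply is that the document never says unknown-place deaths are kept or coded as elsewhere. That follows only from the unqualified words for total deaths in a condensed article. The exclusion rule might be meant to apply throughout work package 2, a full analysis plan is promised under Reporting guidelines, and the ecological section allows other approaches after the data have been examined. This stands as far as intent goes: a reader might infer a deliberate coding of unknowns as non-hospital, and the text does not support that. It does not remove the point. The article gives an explicit formula, and followed as written that formula has this effect. The allowance for other approaches does not redefine the denominator.

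Three further inferences are tempting and go too far:

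- **The EPaCCS effect is biased in a known direction.** The downward shift applies to the level of the rate. Equal missingness only attenuates the slope, and unequal missingness can move it either way.
- **Any disagreement between the two analyses would come from this rule.** They already differ by design: the individual-level cohort is limited to four disease groups and is weighted, while the ecological rates use all deaths.
- **Excluding unknowns wastes information that the acute data already hold.** Table 1 says "The WSIC dataset includes coded primary, secondary, acute, mental health, community health and social care data", but no discharge-disposition field is described, and excluding missing outcomes is a common choice.

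**Conclusion.** The point holds as an inconsistency between two stated rules for the primary outcome. The ecological formula, taken literally, counts deaths of unknown place as non-hospital. Its level is then too low by qm, and the EPaCCS slope is attenuated by the fraction m if missingness is constant and equal in both groups. Missingness that differs by EPaCCS status, or that trends with coverage over 2010–2023, could shrink or inflate the slope.

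The size cannot be stated, because no missing fraction is given; the illustrations assume m between 1% and 10%. If place of death is close to complete in the linked data, the effect is negligible. The document therefore does not support a claim of material or directional bias in the EPaCCS effect. It supports a cheap correction of the denominator and a check on missingness. The individual-level formula is not affected.

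**What to change.** 1. In Ecological analysis, define the hospital-death rate as in-hospital deaths over deaths with known place, in line with Missing data considerations. Keep total deaths as the denominator of the EPaCCS coverage rate and of time in hospital.
2. Tabulate unknown place of death by borough-year and EPaCCS status.
3. Bound the ecological result by assigning all unknowns to hospital and then all to elsewhere. This is needed because the known-place rate is itself unbiased only if unknowns resemble the rest.
4. If acute admission records are used to resolve unknowns, do so as a sensitivity analysis. Class every unknown death as in hospital if an admission was open at death and otherwise as elsewhere, and keep them all in the denominator. Do not recover hospital deaths only and then drop the rest.

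The cost is about one sentence in the ecological section, one table and two bounding runs. The optional sensitivity analysis adds one derivation from admission data that the plan already uses for time in hospital. No new data are needed.
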